## Abstract

**Background:**

Major depressive disorder (MDD) is the second highest cause of disability worldwide. Standard treatments for MDD include medicine and talk therapy; however, approximately 1 in 5 Canadians fail to respond to these approaches and must consider alternatives. Transcranial direct current stimulation (tDCS) is a safe, noninvasive method that uses electrical stimulation to change the activation pattern of different brain regions. By targeting those regions known to be affected in MDD, tDCS may be useful in ameliorating treatment-resistant depression.

**Objective:**

The objective of the Neurostimulation of the Brain in Depression trial is to compare the effectiveness of active versus sham tDCS in treating patients with ultraresistant MDD. The primary outcome will be the improvement in depressive symptoms, as measured by the change on the Mongtomery-Asberg Depression Rating Scale. Secondary outcomes will include changes in the Quick Inventory of Depressive Symptomatology Scale (subjective assessment), the World Health Organization Disability Assessment Schedule 2.0 (functional assessment), and the Screen for Cognitive Impairment in Psychiatry (cognitive assessment). Adverse events will be captured using the Young Mania Rating Scale; tDCS Adverse Events Questionnaire; Frequency, Intensity, and Burden of Side Effects Rating Scale; and Patient-Rated Inventory of Side Effects Scale. A parallel component of the study will involve assaying for baseline language function and the effect of treatment on language using an exploratory acoustic and semantic corpus analysis on recorded interviews. Participant accuracy and response latency on an auditory lexical decision task will also be evaluated.

**Methods:**

We will recruit inpatients and outpatients in the city of Edmonton, Alberta, and will deliver the study interventions at the Grey Nuns and University of Alberta Hospitals. Written informed consent will be obtained from all participants before enrollment. Eligible participants will be randomly assigned, in a double-blinded fashion, to receive active or sham tDCS, and they will continue receiving their usual pharmacotherapy and psychotherapy throughout the trial. In both groups, participants will receive 30 weekday stimulation sessions, each session being 30 minutes in length, with the anode over the left dorsolateral prefrontal cortex and the cathode over the right. Participants in the active group will be stimulated at 2 mA throughout, whereas the sham group will receive only a brief period of stimulation to mimic skin sensations felt in the active group. Measurements will be conducted at regular points throughout the trial and 30 days after trial completion.

**Results:**

The trial has been approved by the University of Alberta Research Ethics Board and is scheduled to commence in June 2021. The target sample size is 60 participants.

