### Intervention and Control

In addition to continuing their usual pharmacological and psychological treatments, participants in both arms will receive 30 sessions of either sham or active tDCS, 5 days per week, for a total of 6 weeks, using a Sooma stimulator (Sooma Oy). This constitutes twice the number of treatment sessions as that used in the longest previously conducted study of tDCS in treatment-resistant depression [20]. For both groups, the anode will be positioned over the left DLPFC (position F3 on the 10-20 EEG system), and the cathode will be positioned over the right DLPFC (position F4). Electrodes will be positioned using the caps supplied by Sooma, with participant head circumference measured first to ensure that the proper-sized cap is applied. Each electrode pad will be saturated with 15 mL of normal saline before application.

Participants will be blinded to the group to which they have been assigned. Two stimulators labeled only as *A* and *B* will be set to provide either sham or active stimulation by an investigator not involved in participant interaction or data collection. In the sham group, the applied current will ramp up from 0.3 mA to 2 mA over 17 seconds and then ramp down to 0.3 mA over 17 seconds, where it will be maintained for the duration of the 30-minute session. Previous trials have demonstrated that this short period of active stimulation is an effective way of triggering scalp tingling at a total dose of tDCS believed to be below the threshold for inducing neuroplasticity changes [32,33]. Current must be maintained at 0.3 mA to allow for operation of the electrode-contact sensors; if these were deactivated entirely, blinding would be broken. In the active intervention group, the applied current will ramp up to 2 mA over 17 seconds and be maintained at that level for 30 minutes, before gradually ramping down.

Participants will be withdrawn from the study if they miss two consecutive treatments or more than five treatments in total, if they undergo a serious adverse event or clinical deterioration (which may include new-onset psychosis, severe suicidal ideation, or a manic or hypomanic switch), or if they or their treating psychiatrist wish them to be withdrawn.

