### Data Analysis and Sample Size Calculations

The primary and secondary efficacy outcomes will be analyzed using a mixed effects repeated measures ANOVA (analysis of variance), with the study group and time as fixed factors and participants as random factors, based on the intention to treat principle. Due to the wide variety of potential adverse events that can be captured, we will present this information as frequency data.

To detect a moderate effect size for the primary outcome, represented by a Cohen *f* of 0.25, with a power of 80% and significance ⍺=.05, we estimate that 60 participants will need to complete the protocol. This assumes a moderate correlation (*r*=0.3) between time points, using the power curves described in the textbook by Kirk [46]. As a study of this scope, in the ultraresistant MDD population, has not been performed before, we are unable to estimate the dropout rate. We plan to conduct an interim analysis after 30 participants complete the protocol. We will analyze the main effects of the treatment by presenting the significance of the time, treatment group, and interaction terms in the ANOVA. If there is a significant interaction, we will conduct posthoc comparisons between mean treatment and placebo outcome scores, at each time point, to characterize this effect further and will use the Tukey method to control the familywise error rate.

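### Sixty is given both as the target sample and as the number who must complete, so the stated 80% power is not the power of a trial that randomises 60

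*Protocol article*

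**What the plan says.** - **Abstract, Results:** "The target sample size is 60 participants". It does not say whether these are people randomised or people completing.
- **Methods, Data Analysis and Sample Size Calculations:** the effect is "represented by a Cohen *f* of 0.25", "with a power of 80% and significance" level .05, and "we estimate that 60 participants will need to complete the protocol". A correlation of 0.3 between time points is assumed. On attrition, "we are unable to estimate the dropout rate", and nothing is added for it. The same section specifies a mixed-effects repeated measures ANOVA on the intention-to-treat principle.
- **Methods, Intervention and Control:** participants leave the study if they "miss two consecutive treatments or more than five treatments in total". They also leave after a serious adverse event or clinical deterioration, or at their own or their psychiatrist's wish.
- **Discussion, Limitations:** daily travel to the hospital is named as a possible compliance problem for outpatients, while the burden on inpatients is called minimal.

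The article gives no larger enrolment figure and no rule to keep recruiting until 60 have completed.

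**The concern.** One number stands for two quantities. A target of 60 participants and a requirement of 60 completers match only if every participant finishes 30 weekday sessions and the follow-up one month later. The protocol itself sets out several routes by which participants will be withdrawn. Not knowing the dropout rate is a reason to show a range; it does not support an allowance of zero.

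A reader will take 80% as the power of a trial that randomises 60. If 60 is the number randomised, that figure is too favourable by an amount that depends on attrition and on how partial data are used. If 60 is the number completing, the article does not say how many will be randomised.

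**Working it through.** **Inputs.** From the sample size section: f = 0.25, α = .05, r = 0.3, power 80%, 60 completers. From Trial Design: 1:1 allocation. From Data Collection: assessments at T0, T10, T20, T30 and T60, so m = 5 visits, or m = 4 after baseline. The powered ANOVA term and the number of visits used are not stated. No dropout rate is given, so 10%, 20% and 30% are my assumptions.

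**Step 1: reproduce the 60.** For a between-group effect averaged over m visits, the noncentrality is λ = f²·N·m / [1 + (m − 1)r], with 1 and N − 2 degrees of freedom.

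- m = 5, N = 60: λ = 0.0625 × 60 × 5 / 2.2 = 8.52, power 81.9%. The smallest N reaching 80% is 58.
- m = 4, N = 60: λ = 0.0625 × 60 × 4 / 1.9 = 7.89, power 78.9%. The smallest N reaching 80% is 62.

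Both fall within two participants of the stated 60. Other readings do not. The group-by-time interaction under the usual convention, λ = f²·N·m / (1 − r), needs 28 (m = 5) or 32 (m = 4). A single-visit comparison at d = 0.5 needs 128 by F test.

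**Step 2: 60 randomised, only completers counted.**

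| Assumed loss | Completers | Power, m = 5 | Power, m = 4 |
|---|---|---|---|
| 0% | 60 | 81.9% | 78.9% |
| 10% | 54 | 77.6% | 74.4% |
| 20% | 48 | 72.5% | 69.2% |
| 30% | 42 | 66.4% | 63.1% |

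Near the top, with m = 5: 59 completers give 81.2%, 58 give 80.5% and 57 give 79.8%.

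**Step 3: 60 randomised, partial data kept by the mixed model.** A person with k visits carries information proportional to I(k) = k / [1 + (k − 1)r]. So I(2) = 2/1.3 = 1.538, I(4) = 4/1.9 = 2.105 and I(5) = 5/2.2 = 2.273. With a fraction d lost after two assessments, the effective N is 60 × [(1 − d) + d·I(2)/I(m)]. The degrees of freedom stay at 1 and 58.

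| Assumed loss | Effective N, m = 5 | Power, m = 5 | Effective N, m = 4 | Power, m = 4 |
|---|---|---|---|---|
| 10% | 58.1 | 80.6% | 58.4 | 77.8% |
| 20% | 56.1 | 79.3% | 56.8 | 76.7% |
| 30% | 54.2 | 77.9% | 55.2 | 75.5% |

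This assumes the same group difference at each counted visit, a common correlation of 0.3, and loss unrelated to outcome.

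**Step 4: how much loss the missed-session rule could cause.** The documents give no miss rate. Suppose sessions are missed independently over 30 sessions, and withdrawal follows two consecutive misses or a sixth miss in total. The rule then removes about 1% of participants at a 2% miss rate, 7% at 5%, 25% at 10% and 50% at 15%. The result depends almost wholly on the assumed rate.

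**Step 5: enrolment if 60 must complete.** 60/(1 − d), rounded up, gives 67, 75 and 86 at 10%, 20% and 30% loss (68, 76 and 86 as even numbers for 1:1).

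**The case against.** **The abstract's 60 may mean completers.** It is one short sentence. The sample size section counts completers throughout, including for the interim analysis, so the two sixties could agree. This is a fair reading, but it leaves the article with no number to randomise. Some clarification is needed either way.

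**A reader might infer that any loss takes power below 80%.** The calculation does not support this. With five visits, two losses still leave 80.5%. With four visits, power is already 78.9% with no loss at all.

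**A reader might take 78%, 73% and 66% as the trial's power.** They are not. They discard everything from participants who leave, while the plan specifies an intention-to-treat mixed model that can use earlier assessments. At 20% loss with two assessments each, the five-visit figure is 79.3% and not 72.5%. This objection stands, and the completers-only figures serve only as a worst case.

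**The powered term is not named.** Under the usual interaction convention with five visits, 60 participants give about 99% and 42 still give about 95%, so no plausible loss would matter. That reading needs only about half of the stated 60, so it is unlikely to be the calculation used. The between-group reading nevertheless remains an inference.

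**A reader might infer that the missed-session rule will remove a quarter of participants.** That holds only at an assumed 10% miss rate. At 2% it is about 1%. Inpatients, for whom the protocol expects little burden, are also recruited.

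**Conclusion.** The point holds in a limited form. The target and the requirement are the same number, no loss is allowed for, and the protocol provides for loss. The stated 80% therefore cannot be read as the power of a trial that randomises 60.

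The shortfall may be small. At 10–30% assumed loss, the five-visit between-group reading gives roughly 78% to 81% if two assessments per lost participant are kept. It gives 66% to 78% if only completers count. Four visits give about three points less. These figures rest on an inferred powered term and visit count, assumed loss rates, and loss unrelated to outcome. The mismatch between the two sections rests on none of these assumptions.

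**What to change.** 1. In the abstract and in the sample size section, say whether 60 is the number randomised or the number completing, and use the same wording in both.
2. If 60 are randomised, replace the single 80% with power over an assumed 10–30% loss. Compute it for a named primary contrast, with the number of visits stated, under the planned intention-to-treat mixed model. Give completers-only power beside it, labelled as the worst case.
3. If 60 must complete, give the enrolment number over the same range: 67, 75 and 86 at 10%, 20% and 30% loss.
4. If the effect of the missed-session rule is discussed, show it over a range of assumed miss rates and not as one figure.

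With 60 randomised, the cost is a short recalculation and a rewording. The stated power may look less favourable, and no participants are added. Keeping 60 completers would cost 7 to 26 more participants over that loss range.

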**Conclusions:**

This is a protocol for a multicenter, double-blinded, randomized controlled superiority trial comparing active versus sham tDCS in patients with treatment-resistant MDD.

**Trial Registration:**

ClinicalTrials.gov NCT04159012; http://clinicaltrials.gov/ct2/show/NCT04159012.

**International Registered Report Identifier (IRRID):**

PRR1-10.2196/22805

## Introduction

### Depression

As delineated in the *Diagnostic and Statistical Manual of Mental Disorders, Fifth Edition*, major depressive disorder (MDD) is characterized by the occurrence, and often recurrence, of major depressive episodes [1]. During these times, patients have low mood and/or anhedonia, in addition to at least four other criteria-specific symptoms encompassing emotional, cognitive, and somatic realms, for at least 2 weeks. MDD is a chronic, debilitating mental illness that exerts a profound effect on the quality of life of patients. Taken as a whole, depression is the second highest cause of disability both worldwide and in Canada, with an annual prevalence of 4.3% and a lifetime prevalence of 11.7% [2]. The resultant cost to Canada’s economy—from both direct and downstream effects—is a similarly high Can $32.3 billion (US $25.6 billion) annually, which is 2% of the nation’s gross domestic product [3]. Patients with depression have a 1.5-fold higher mortality rate and a 20-fold higher rate of completed suicide than their nondepressed counterparts [4,5].

Given its immense personal and societal impact, adequate treatment of depressive episodes is of utmost importance. From a physiological perspective, MDD likely arises from an imbalance in the activity of different neuronal circuits, leading to impairments in emotion regulation, social appraisal, cognitive functioning, and a variety of other mental domains [6]. All treatments, be they psychotherapeutic, pharmacological, or neuromodulatory in nature, function by restoring and ideally maintaining balanced neuronal function. Owing to their cost-effectiveness and ease of administration, medication and psychotherapy are first-line treatments for most subtypes of depression; however, 1 in 5 Canadians with MDD are deemed to have treatment-resistant depression that does not adequately respond to either of these modalities [7].

For these patients, the treatment of choice has traditionally consisted of electroconvulsive therapy (ECT), which was first pioneered in 1938 [8]. Although refinements to the procedure have been made since then, the general premise remains the same—by applying a brief, high-intensity electrical stimulus to the brain, one can induce a short seizure that treats depression through a variety of mechanisms [9]. Such treatments are given as a series of 6-16 sessions, in a highly monitored setting, and typically to inpatients in psychiatric facilities. Although effective, this method of neuromodulation has several limitations. From a health systems standpoint, it is expensive, time consuming, and resource intensive, requiring the services of a psychiatrist, anesthesiologist, and a variety of acute care allied health staff. As such, only specialized facilities routinely offer ECT, which can limit its utility in rural areas. Moreover, it can exert a deleterious effect on the cognitive function of patients during the course of treatment [10]. Even if patients do not experience significant side effects, the requirements of the treatment can impose a high iatrogenic burden. Many individuals are voluntarily hospitalized during their course of ECT, which can last a month or longer and can induce further disruption in their occupational and interpersonal lives. Others still choose not to even pursue ECT owing to their preconceived notions and the high stigma attached to it as a result of its portrayal in popular media [11,12].

### Transcranial Direct Current Stimulation

Options for treatment in individuals with refractory depression are limited, especially if they cannot pursue or have had no response to ECT. One promising method of neuromodulation that may be used in this scenario is transcranial direct current stimulation (tDCS). Unlike ECT, which uses a brief, high-intensity stimulus to induce seizures, tDCS consists of the application of a low-intensity current for longer periods (typically 20 to 30 minutes) through electrodes that are applied to the scalp. No seizures are generated, and as such, there is no need for general anesthesia or intensive monitoring; patients may even complete the treatment at home. The device itself, which is fairly simple from a mechanical perspective, is also cost-effective and can be purchased for less than Can $1000 (US $790). This compares favorably with ECT and with other neuromodulatory therapies such as repetitive transcranial magnetic stimulation (rTMS), which costs up to Can $75,000 (US $59,000) to purchase.

The mechanism by which tDCS exerts its effects is still under study. In part, it may induce long-term potentiation (LTP) and long-term depression (LTD), the mechanisms underlying neural plasticity, in targeted regions of the brain and modulate the activity of neural circuits without generating action potentials. Current flowing out of the anode may induce LTP and increase neuronal activity, whereas current flowing into the cathode may induce LTD and decrease brain activity [13]. Most studies of tDCS in the treatment of depression have applied anodal stimulation over the left dorsolateral prefrontal cortex (DLPFC) and cathodal stimulation over the right DLPFC—areas of the brain which are known to be hypometabolic and hypermetabolic, respectively, in patients with depression [14]. Due to its targeted nature, tDCS has not been shown to adversely affect cognition and may actually improve cognitive function over the course of treatment [15]. Electrodes can be accurately positioned by surface scalp measurement alone, and neuroimaging-guided localization is not required.

Previous studies have shown that tDCS is a safe and effective treatment for a variety of neuropsychiatric disorders, including schizophrenia, chronic pain, dementia, poststroke rehabilitation, and depression [16,17]. A meta-analysis by Brunoni et al [18], which examined 6 randomized control trials and a total of 289 patients with MDD, found that active tDCS was significantly superior to sham tDCS with respect to both response to treatment (odds ratio [OR] 2.44; number needed to treat [NNT]=7) and the induction of remission (OR 2.38; NNT=9) [18]. These results are similar to those observed for other therapies such as high-frequency rTMS, which has NNTs of 6 and 8 for response and remission, respectively [19].

These results suggest that tDCS may be an effective treatment for MDD; however, its role in treating more refractory cases remains unclear. The meta-analysis by Brunoni et al [18] found that the likelihood of response to tDCS was positively correlated with treatment duration and dose but negatively correlated with treatment resistance (defined as a failure to respond to 2 previous trials of antidepressants). This mirrors the findings seen with other neuromodulation techniques, including ECT and rTMS, and implies that patients with treatment resistance may need to be treated with higher-intensity protocols than their nonresistant counterparts. However, to date, only 3 studies have specifically examined tDCS in patients with treatment-resistant depression, and all have been limited by small sample sizes and relatively low-intensity protocols, among other methodological issues [20-22]. Unsurprisingly, these studies failed to demonstrate the effectiveness of tDCS, yet it remains unclear whether this is truly because of a lack of efficacy or because of issues with study design.

### Safety

In a meta-analysis examining over 33,200 sessions of tDCS, no serious adverse events were identified [23]. Common side effects of treatment that occur in up to 50% of patients include mild-to-moderate skin erythema, itchiness, tingling at electrode sites, or mild headache [20,24]. Less commonly observed side effects that have been reported include tinnitus, nervousness, light-headedness, blurred or brighter vision, reduced concentration, nausea, mild euphoria, fatigue, insomnia, or constriction when swallowing. When they occur, these side effects are generally transient and of low intensity.

In patients with bipolar depression, tDCS may rarely induce a manic or hypomanic switch. In a randomized control trial evaluating the use of tDCS in bipolar depression, treatment-emergent affective switches were observed in 15% of patients; however, these did not meet the criteria for hypomanic or manic episodes and did not require hospitalization or treatment discontinuation [25].

### Objectives

The main objective of this study is to compare the effectiveness of active versus sham tDCS in ameliorating depressive symptoms in participants with ultratreatment-resistant MDD. We have operationally defined ultraresistant MDD to include depression that has failed to remit despite the use of ketamine, ECT, or at least five previous antidepressant trials at clinically effective doses. The secondary objectives of the study are to compare the safety of active versus sham tDCS and their respective effects on the speech and language abilities of participants.

## Methods

### Trial Design

The Neurostimulation of the Brain in Depression (NESBID) trial is a pragmatic, randomized, parallel group, participant- and investigator-blinded multicenter superiority trial. Participants will be randomized in a 1:1 fashion between active and sham tDCS and will continue to receive their usual treatment, including pharmacological and psychological therapies, during the course of the trial.

